## Abstract

**Background:**

Five-year survival on dialysis is only 40%, compared to 74% with a deceased donor kidney transplant (DDKT) and 87% with a living donor kidney transplant (LDKT). An American Society of Transplantation (AST) Consensus Conference recommended that patients with chronic kidney disease (CKD) Stages 3–5 have the opportunity to learn about and decide which treatment option is right for them, particularly about LDKT. However, early education about LDKT and DDKT outside of transplant centers is inconsistent and often poor, with patients in CKD 3 and 4 and ethnic/racial minorities even less likely to receive it. A new randomized control trial (RCT), in partnership with Kaiser Permanente Southern California (KPSC), will assess knowledge gaps and the effectiveness of a supplementary video-guided, print and technology-based education intervention for English- and Spanish-speaking patients in CKD Stages 3, 4, and 5 to increase LDKT knowledge and decision-making. To date, no published LDKT educational interventions have studied such a large and diverse CKD population.

**Methods:**

In this RCT, 1200 English and Spanish-speaking CKD Stage 3–5 patients will be randomly assigned to one of two education conditions: *ET@Home* or KPSC standard of care education. Randomization will be stratified by CKD stage and primary language spoken. Those in the *ET@Home* condition will receive brochures, postcards, DVDs, and text messages delivering educational content in modules over a six-month period. Baseline data collection will measure demographics, transplant derailers, and the amount of previous CKD and transplant education they have received. Changes in CKD and transplant knowledge, ability to make an informed decision about transplant, and self-efficacy to pursue LDKT will be captured with surveys administered at baseline and at six months.

**Discussion:**

At the conclusion of the study, investigators will understand key knowledge gaps for patients along the CKD continuum and between patients who speak different languages and have assessed the effectiveness of both English- and Spanish-language supplementary education in increasing KPSC patients’ knowledge about the opportunities for and risks and benefits of LDKT. We hope this program will reduce disparities in access to transplant.

**Trial Registration:**

ClinicalTrials.gov Identifier: NCT03389932; date registered: 12/26/2017.

## Background

There are 30 million Americans with chronic kidney disease (CKD) and at risk for kidney failure, and 660,000 patients with end-stage renal disease (ESRD). To sustain life, ESRD patients, 31% of whom are Black, 15% Hispanic, and 5% Asian, must either receive daily or weekly dialysis treatments or have a kidney transplant. The five-year survival rate for patients on dialysis is only 40%, compared to 74% for patients who receive a deceased donor kidney transplant (DDKT) and 87% for patients who receive a living donor kidney transplant (LDKT) [1]. Over 95,000 individuals are awaiting a DDKT in the United States, with more being added daily (based on OPTN data as of 06/08/2018).

Patients who receive kidney transplants live 5–15 years longer than if they remained on dialysis and have a better health-related quality of life (HRQOL), including a greater likelihood of being in the workforce during their critical earning years [2]. While LDKT is the medically optimal and most cost-effective renal replacement therapy (RRT) for patients with ESRD, LDKT rates have declined by 17% from 2004 to 2014. In 2014, in the U.S., 17,106 patients received a transplant (5536 LDKTs) while 8021 patients died or became too ill to remain on the list; 70% who died were racial/ethnic minorities. Of the 2281 transplants performed in California in 2017, only 604 were from living donors (OPTN data as of 06/08/2018).

Providing comprehensive education to CKD patients about the benefits of LDKT as early as possible can increase the chances that they will learn about it, seek living donors, and ultimately receive an LDKT [3]. Many patients, particularly socioeconomically disadvantaged patients and patients of racial/ethnic minority groups [4], have not had sufficient DDKT and LDKT education before their kidneys failed. [5, 6] Generally, patients not considering LDKT lack knowledge about the benefits of living donation over remaining on dialysis [7], have concerns about involving and risking a living donor’s health [7], fear asking others to donate a kidney [8], or fear their own surgical pain and the possibility of the transplanted kidney failing [9].

While Black and Hispanic patients experience higher rates of diabetes and hypertension [5] and increased chances of developing ESRD versus their White or non-Hispanic counterparts [10], they are less likely to complete transplant evaluation [6, 11, 12], experience longer wait-list times [13, 14], and are less likely to receive a DDKT or LDKT [6, 10, 15, 16]. While 11.4% of White patients had received an LDKT after two years of being wait-listed, only 2.9 and 5.9% of Black and Hispanic patients, respectively, had received an LDKT [11, 17]. The disparity in transplant knowledge between White patients and patients of racial or ethnic minorities has been well documented by our research team [7, 8, 18, 19].

Without a nationally coordinated healthcare system in the United States, it is difficult to ensure that patients moving from CKD Stages 3 and 4 to ESRD are consistently making informed transplant decisions. Limited research is available about how transplant education for patients in CKD Stage 3 and 4 is delivered. One study in community nephrologist’s offices, the Talking About Live Kidney Donation (TALK) program, compared the efficacy of an LDKT print and video program, with or without in-person social worker discussions, on CKD patients’ steps toward beginning transplant evaluation [20]. Though the TALK trial found that the discussion-oriented, social worker intervention had a higher predicted probability of taking additional steps in comparison to the education-only group, it also found that significantly higher proportions of patients in the education-only group took key steps towards transplant, like completing transplant evaluation.

Effective strategies for transplant education within dialysis centers are important to understand since 70% of ESRD patients are on dialysis [21], some of whom may never present to a transplant center for evaluation. Our team surveyed dialysis educators at 170 dialysis centers and found that 81% of educators were educating patients by recommending that they learn more about transplant by going to a transplant center or learning about transplant themselves [22]. In another study, only 24% (297 of 1223) of “informed” patients (based on patient-reported data submitted to the Centers for Medicare and Medicaid Services on Form-2728) reported that educators had detailed discussions about the risks and benefits of DDKT and LDKT with them [22]. Other similar studies have found that less than half of dialysis patients receive comprehensive discussions or counselling about the risks and benefits of transplant [22]. Our previous research has also shown that while kidney patients spend over 500 h in the dialysis center annually, they only spend a median of one hour reading brochures about transplant and 30 min talking about transplant with medical staff [4]. Only a minority of dialysis centers have formal education programs or provide transplant education to share with potential living donors [22–24]. For these and many other reasons, evidence suggests that not all dialysis patients receive appropriate information about transplant [5, 6, 22, 23, 25].

Previous research has shown that two of the strongest predictors of successful completion of transplant evaluation are having access to more transplant education resources and having greater transplant knowledge at the onset of transplant evaluation, the latter also being the only significant predictor for ultimately receiving an LDKT [26]. With providers outside of transplant centers reporting constraints to educating patients about transplant [23], it is possible that providing supplementary education within a large health care system, with its fully integrated care management program, may be an opportune way to efficiently educate more CKD 3–5 patients about the opportunities for and risks and benefits of DDKT and LDKT. Further, the use of technology, such as text messaging, videos, and digital applications may reduce the provider burden barrier to delivering transplant education.

There is previous evidence that delivering more comprehensive education over time may be helpful to patients making informed decisions outside of transplant centers. The RaDIANT program in Georgia which targeted dialysis providers and patients with a multi-component educational intervention including patient educational toolkits, videos, and a transplant mentoring program over one-year found a 75% increased adjusted odds of referral for kidney transplant evaluation and that the intervention activities were more effective for Black versus White patients [27]. Through a group randomized controlled trial, a version of *Explore Transplant (ET)* delivered face-to-face over four meetings with patients while they were undergoing dialysis, was shown to increase patients’ knowledge and informed decision-making significantly more than standard transplant education offered in dialysis centers [28]. Finally, *Explore Transplant@Home* (*ET@Home*) delivered by mail and supported through bimonthly postcards and texting over an eight-month period also found significant increases in transplant knowledge and informed decision-making among ESRD patients who received *ET* in this format, compared with standard transplant education in dialysis centers [29].

To date, *ET* and *ET@Home* have never been studied with patients who are in CKD Stages 3 & 4 or with Asian or Spanish-speaking patients. This study is a partnership between UCLA and Kaiser Permanente Southern California (KPSC). KPSC’s fully integrated care management program, diverse membership, and ability to track a large patient population offers a rare opportunity to study how knowledgeable CKD Stage 3–5 patients are about LDKT, assess disparities in knowledge across many races, ethnicities, and languages, and conduct a large-scale trial of the effectiveness of *ET@Home*. This manuscript will describe the protocol for a new randomized control trial (RCT) conducted in collaboration with KPSC to assess the effectiveness of *ET@Home* within a large healthcare system with a diverse group of CKD 3–5 patients.

## Study design

The purpose of this study is to assess whether the *ET@Home* program can be integrated successfully across a large racially, ethnically, and geographically diverse patient catchment area and to assess its effectiveness to increase knowledge about the risks and benefits of LDKT and increase informed decision-making. The effectiveness of the *ET@Home* program will be evaluated in a randomized controlled trial (RCT) of 1200 Black, Hispanic, Asian, and White patients with stage 3, 4, or 5 CKD. Patients will be randomized to receive: (1) no additional education other than what is provided within KPSC (standard-of-care); or (2) a video-guided, four-part *ET@Home* program delivered by mail and supported through bimonthly postcards and texting over six months. The study has two aims.

### Aim 1

Before intervention, to assess differences in knowledge and decision-making about the opportunities for and risks and benefits of living kidney donation for 1200 CKD Stage 3–5 patients by race/ethnicity and primary language spoken.

#### Hypothesis

*Patients earlier in the CKD continuum, patients who speak Spanish, and non-White patients will have less knowledge about the opportunities for and risks and benefits of living kidney donation and will be making less informed LDKT decisions.*

### Aim 2

To conduct a randomized controlled trial in English and Spanish of *ET@Home* for CKD Stage 3–5 patients to assess its effectiveness to increase LDKT knowledge and decision-making by race/ethnicity and primary language spoken as compared to the standard KPSC education.

#### Hypothesis 1

*At the conclusion of the trial, CKD patients who receive ET@Home will have greater transplant knowledge and be more likely to make an informed treatment decision than patients receiving KPSC education alone.*

#### Hypothesis 2

*ET@Home will be more or equally effective for patients earlier in the CKD continuum, patients who speak Spanish, and non-White patients than patients in these subgroups receiving KPSC education alone.*

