### Evaluation and statistical analysis plan

#### Power analysis

Based on the following assumptions, we estimated the sample size for the RCT. Using data from previous RCTs [4, 35], a mean knowledge change score of 1.0 points is estimated necessary to be detected among patients receiving *ET@Home* and standard KPSC education. Patients’ baseline transplant knowledge scores will be correlated with those of other patients from the same clinics [intraclass correlation coefficient (ICC) of 0.31]. The variance in knowledge change has both between- and within-cluster components, yielding a pooled standard deviation estimate of 4.0. Participant retention will be 50% at the 6-month assessment. Outcomes will be assessed using two-tailed statistical tests. Type 1 error rate (alpha level) will be set at 0.05. This study design will ensure power of 0.90. Power calculations for this trial are based on all of these factors, which yields a standardized effect size, accounting for clustering of approximately 0.257.

Power analyses based on changes in transplant knowledge, our primary study outcome, are presented. The study design and analyses were treated as a test of the difference between the mean knowledge score change of CKD patients in the *ET@Home* and standard KPSC education (control) conditions six months post-baseline. It is estimated that with 600 completed surveys (50% attrition), there will be a 90% power to detect a 0.25 effect size between two equal-sized groups (control and treatment groups). By stratifying recruitment and randomization by race/ethnicity (Asian, Black, Hispanic, White), primary language spoken (English vs. Spanish), and stage of CKD, according to the table below, this sample size will also have 90% power to detect 1 point differences in change on the transplant knowledge scale between the *ET@Home* and standard KPSC education conditions for these critical subgroups using interaction terms (e.g., treatment by race interaction, language by race interaction). Patients enrolled and randomized are shown in Table 3.

**Table 3 Tab3:** Patients enrolled and randomized

Race/Ethnicity/Language	Stage of CKD			
	3^a^	4	5/ESRD	Total
*English-speaking Asian*	67	67	66	200
*English-speaking Black*	67	66	67	200
*English-speaking White*	67	67	67	200
*English-speaking Hispanic*	67	67	66	200
*Spanish-speaking Hispanic*	133	133	134	400
Total	400	400	400	1200

^a^
*CKD* 3 patient recruitment prioritized based on likelihood to progress

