Next, the effectiveness of *ET@Home* for CKD Stage 3–5 patients to increase LDKT knowledge and decision-making compared to KPSC education, by race/ethnicity and primary language spoken, will be evaluated. First, it will be determined if baseline differences in patient- and clinic-level variables are present using χ2 and Wilcoxon rank-sum tests, and subsequently adjustments for any out-of-balance characteristics in outcome analyses will be made. Differences in changes in transplant knowledge and Self-Efficacy using change scores, defined as the difference between the baseline and post-survey assessments, will be examined. Differences in these outcomes between the educational conditions will be tested using multilevel random effects models with normal outcome distributions, accounting for clustering with a random intercept for CKD clinic. Differences in informed decision-making will be examined using multilevel random effects logistic models. Finally, for the number of new steps taken, differences between the educational conditions in the count of new steps will be analyzed with a multilevel random effects Poisson model.

After the primary analyses are completed, multilevel random effects models will be constructed to examine the heterogeneity of treatment effect (HTE) using interaction terms for the *ET@Home* educational condition by the key patient subgroups by which randomization was stratified, including race, primary language spoken, and stage of CKD. For example, the *ET@Home* educational condition (*ET@Home* vs. SOC) x primary language (English vs. Spanish) interaction term will be tested, enabling us to determine of the *ET@Home* intervention was more or less effective for primarily Spanish-speaking patients than English-speaking patients.

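### Hypothesis 2 and its planned interaction test address different contrasts, neither can establish equal effectiveness, and the 90% subgroup power claimed for the interaction tests is about 21–30%

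*Protocol article*

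**What the plan says.** Three parts of the protocol article bear on this point.

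- **Aim 2, Hypothesis 2.** ET@Home "will be more or equally effective for patients earlier in the CKD continuum", for Spanish speakers and for non-White patients, "than patients in these subgroups receiving KPSC education alone". The comparator is the control arm of the same subgroup. No margin is attached to equality. The Outcome measures section likewise speaks of comparing the two conditions for these patients.
- **Statistical analysis.** After the primary analyses, multilevel models are to be built "to examine the heterogeneity of treatment effect (HTE) using interaction terms for the" treatment condition by race, language and CKD stage. The worked example asks whether ET@Home "was more or less effective for primarily Spanish-speaking patients than English-speaking patients".
- **Power analysis.** "Outcomes will be assessed using two-tailed statistical tests", and "Type 1 error rate (alpha level) will be set at 0.05". For the subgroups, the section states that "this sample size will also have 90% power to detect 1 point differences in change" between the arms, using interaction terms. One of its two examples, language by race, contains no treatment term.

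**The concern.** The hypothesis and the test do not describe the same quantity.

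- **Within-subgroup reading (the literal one).** The question is whether ET@Home beats KPSC education among, say, Spanish speakers. Counting equality as success means that an intervention with no effect in that group would confirm the hypothesis. Hypothesis 1, by contrast, requires greater knowledge than control.
- **Between-subgroup reading (the one the analysis section implies).** The question is whether the effect in Spanish speakers is at least as large as in English speakers. The interaction is then the right contrast, but a two-sided difference test can support only a difference. The article gives no margin or confidence-interval criterion that would let it support equality.

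The article says that ET@Home has not been studied in CKD stages 3 and 4 or in Asian or Spanish-speaking patients, so the subgroup findings are a main product of the trial. The 90% power statement adds to the risk: a reader who trusts it would take a non-significant interaction as good evidence that effects are similar. That inference depends on how precise the interaction estimate will be.

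**Working it through.** **Inputs.** From Power analysis: target difference 1.0 point, SD of change 4.0, 600 completers of 1200 (50%), two-sided alpha 0.05, ICC 0.31. From the randomization section: 1:1 allocation. From Table 3 (randomized): Spanish-speaking 400, English-speaking 800; White 200, non-White 1000; 400 in each CKD stage. Assumed: 50% retention in every stratum, equal SD across strata, and no further inflation for clustering, because the article says its effect size already accounts for it.

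Completers per arm: Spanish 100, English 200; stage 3 100, stages 4/5 200; White 50, non-White 250.

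**Step 1: the plan's overall figure.** With 300 per arm, SE = 4 × √(2/300) = 0.327 and power = Φ(1/0.327 − 1.96) = Φ(1.10) = 86.5%. At the article's standardized effect of 0.257, power is Φ(0.257/√(2/300) − 1.96) = Φ(1.19) = 88.3%. The overall claim is nearly reproduced.

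**Step 2: interactions.** SE = SD × √(2/a + 2/b), where a and b are completers per arm in the two subgroups; power = Φ(1/SE − 1.96).

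- Language, or stage 3 vs 4/5: SE = 4 × √(2/100 + 2/200) = 0.693; half-width 1.96 × 0.693 = 1.36; power Φ(1.443 − 1.96) = 30%.
- Non-White vs White: SE = 4 × √(2/250 + 2/50) = 0.876; half-width 1.72; power Φ(1.141 − 1.96) = 21%.

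So if ET@Home gained 1 point in English speakers and nothing in Spanish speakers, the interaction would be non-significant about 70% of the time. The corresponding figure for non-White vs White is 79%.

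**Step 3: sensitivity.** The SD of 4.0 contains between-clinic variance, and the analysis fits a clinic random intercept. If the ICC of 0.31 applied to change scores (an assumption, since the article gives it for baseline knowledge), the within-clinic SD would be 4 × √(1 − 0.31) = 3.32.

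| Contrast | SD | Half-width | Power, 1 point |
|---|---|---|---|
| Language; stage 3 vs 4/5 | 4.0 | 1.36 | 30% |
| Language; stage 3 vs 4/5 | 3.32 | 1.13 | 41% |
| Non-White vs White | 4.0 | 1.72 | 21% |
| Non-White vs White | 3.32 | 1.43 | 28% |

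All four half-widths exceed the 1.0-point target. The most favourable combination tried (full retention, SD 3.32, one-sided test) reaches 79% for language and 62% for non-White vs White.

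**Step 4: could the 90% refer to within-subgroup comparisons?** SE = SD × √(2/a).

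- Spanish or CKD 3 (100 per arm): SE 0.566, power Φ(1.768 − 1.96) = 42%.
- Black (50 per arm): SE 0.800, power Φ(1.25 − 1.96) = 24%.
- Pooled non-White (250 per arm): SE 0.358, power Φ(2.795 − 1.96) = 80%.

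With SD 3.32 these become 57% (Φ(1/0.470 − 1.96)), 32% (Φ(1/0.664 − 1.96)) and 92% (Φ(1/0.297 − 1.96)). Only the pooled non-White comparison then reaches 90%, and it is not an interaction.

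**The case against.** The strongest reply is that the article never says a non-significant interaction will be taken as equal benefit. A reader might infer that rule, because non-significance is the only route to equality that the described analysis offers. The documents do not support the inference: the analysis section poses a question that runs in both directions, and an interpretation rule could sit in a statistical analysis plan that is not shown. This part of the reply stands. The risk is that the result could be misread, not that the plan commits to misreading it.

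A reader might also conclude that Hypothesis 2 cannot be tested at all. That goes too far. The Outcome measures section provides for comparing the two conditions in these patient groups, and the interaction models yield subgroup-specific effects with intervals. The within-subgroup contrast can be estimated; what is missing is a statement of which contrast the hypothesis means.

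The two faults should also be kept apart. Success with no benefit belongs to the within-subgroup reading. Mistaking non-significance for equality belongs to the between-subgroup reading, under which a null effect in Spanish speakers alongside a gain in English speakers would contradict the hypothesis.

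It is tempting to say that reducing disparities is the trial's purpose. The Study design section gives the purpose as integrating the program and raising knowledge and informed decision-making; reduced disparities is expressed as a hope. Finally, these are secondary analyses, and Hypothesis 1 is untouched. None of this removes the mismatch or rescues the 90% figure.

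**Conclusion.** The concern holds as a mismatch that is printed in the article, not as detail left to an analysis plan. Hypothesis 2 as worded is met by no benefit within a subgroup. Its planned test addresses a different contrast and cannot support equality by failing to reject. The 90% power stated for 1-point subgroup differences through interaction terms is wrong: it is about 30% for language and for stage 3 vs 4/5, and about 21% for non-White vs White. Under the smaller assumed SD it is 41% and 28%. At these sizes a full loss of the 1-point effect in a subgroup would usually go undetected: 70–79% of the time with SD 4.0, and about 59–72% with SD 3.32. The results rest on 600 completers distributed as in Table 3, equal retention and equal SD across strata; the conclusion is unchanged across the variants tried. It should be corrected, but it does not affect the primary comparison.

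**What to change.** 1. State which contrast Hypothesis 2 means and delete *or equally*. For example: ET@Home increases knowledge compared with KPSC education within each of these subgroups.
2. Report subgroup-specific effects and each treatment-by-subgroup contrast with 95% CIs, and state that a non-significant interaction is not evidence of equal effectiveness.
3. Replace the 90% subgroup-power claim with the achieved figures at SD 4.0: about 21–30% for interactions, about 42% within the Spanish-speaking or CKD 3 subgroup, and about 80% for pooled non-White patients. Drop the language-by-race example, which has no treatment term.

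Keeping an equality claim is not realistic at this size. With an illustrative 1.0-point margin (the article gives none), one-sided 0.025, 90% power and truly equal effects, language would need 16 × (1.96 + 1.2816)² × (4/(1/3) + 4/(2/3)) ≈ 3,027 completers, against 600 expected.

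The cost is wording in the protocol and the analysis plan, with no new data or patients. The subgroup claims become more modest. The within-subgroup tests also remain underpowered, apart perhaps from pooled non-White patients, so they should be treated as estimation.
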